## Sessions' stakes:

Cognitive stakes

- Distinguish variables on which we can (not) act
- Identify the decisive variables and the difference of their impact on the CVD
- Evaluate one own RCV from personal data (BP, HDL...)

Activities of the learners:

- => Observation
- => Experimentations
- => Comparisons, analyses
- => Awareness acquiring by everyone of the gap (between the outcome and the optimized total health)
- => Setting relationship with the weakening of the atheroma
- => Calculation of total health (risk RCV)
- => Comparison to a optimized total health and to the total of other patients
- => Measure of the impact of the different actions on the variables CVR.
- => Choice of 2 actions (food, AP) potentially realizable.
- => Awareness of the possibility of increasing the total health
- => Reflection on the realization of actions, in context (social... )
- => Choice or not to keep the actions chosen and followed during 5 years
- => Performance indicators for each learner

The implementation of this comprehensive methodology, including the selection of action areas, the recruitment of educators as well as patients and the implementation of education through the learning nests, will allow a support by:

[figure not shown]

and put  
8-10  
to 3  
months  
  
note

**JE DIMINUE LES SUCRÉS ET J'ARRÊTE LE GRIGNOTAGE**

3

Le sucre est présent dans les aliments sucrés (bonbons, sucre, miel, etc.) et dans les boissons sucrées (sodas, jus de fruits, etc.).

Le grignotage est l'habitude de manger de petites quantités d'aliments tout au long de la journée.

L'action que j'ai choisie va m'aider à modifier :

La nature des aliments que je consomme d'habitude

Ma façon de préparer les repas, de cuisiner

Ma façon de prendre les repas (en famille, seul, en collectivité)

**Activité Physique**

**JE MARCHÉ 30 MINUTES PAR JOUR**

7

Points à gagner

Points gagnés

Total = \_\_\_\_ / \_\_\_\_

Je choisis cette action ☐

- 1 • Assistance in daily management and living with diabetes : the provision for patients of supports understandable and discussed in situation facilitates the appropriation of knowledge over time: the written materials are discovered, approached and negotiated in situation, with the help of the educator. The patient takes the written materials at home, and keeps them carefully for the possibility of organizing the monitoring and the daily management of his diabetes and his life over the long term.
- 2 • Social and emotional support: the methodology of patients and educators recruitment through patients' associations and educational clubs will provide a very strong social and emotional support to patients. The group education methodology will also allow patients to support each other. Indeed, the work in interaction with other students, gives education a dimension allowing a very strong emotional support. The possibility of keeping the written material negotiated and worked in situation (booklets), will disseminate information within the family or/and in the social network of the trained patient (without risk of knowledge transformation, as the booklet is a reference). This possibility increases the number of people informed on the prevention of chronic diseases, prevention of complications but also allow bringing the necessary information to the family and social network of the formed patient which will strengthen the social and emotional support brought to the patient.
- 3 • Linkage to clinical care: The choice of intervention areas for Mali has been done taking into account the areas where the care of patients is complete with: an effective and operational diabetes consultation, medicines available and a dynamic diabetic patients association. In these areas, the approach is integrated. The addition of the education methodology by the educators will represent another step in the care pyramid of diabetes. All health workers of the area will be involved in the implementing and monitoring of the process. In addition to the role of educator, educators will also be trained to accompany patients in health facilities that manage diabetes in the intervention area. All peer educators will receive a tool representing the circuit of the patient in the intervention area and will give them to each patient during the animations. Finally, after the meetings patients may accompany each other in the health system.

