**Method (s) :**

This study will be conducted by a multidisciplinary team that brings together high level skills in research projects and in peer education projects. It will be conducted in one site in one country Mali. This site was chosen because they meet a functional care, access to medicines and a dynamic association of diabetic patients. Peer educators and persons targeted by the project will be recruited through the local association of patients. This association will be a social support that provides on going prevention counseling, education and support services to people who have diabetes. It represents an important link between patients, educators and general medical services. The procedure will start by the training of peer educators who were identified and recruited to facilitate the sessions. Then, the 4 educational sessions: control of cardiovascular risk (blood pressure, waist circumference, smoking, cholesterol, glycaemia), control of Food (balance, fat, carbohydrates), physical activity management, insulin management, will be carried out and patients will be able to:

- Analyze knowledge that appears in various forms, including forms adapted to illiterate patients (colour codes, presence of photos)
- Act on knowledge: the patient observes, makes hypothesis, he experiments, compares, deduces, analyzes, makes relations.
- Work in interaction with other learners, which gives education a social dimension.
- Decide on the implementation of actions taking into account individual, cultural, social, economic context

For each situation, a day of training will be conducted by trained peer educators with theoretical contributions on the issue, practical scenarios, analyzes of the issues out of frame and put in "educational security ". These training days will be implemented with 8-10 patients (1Hour and an half) and the 4 sessions will take place over a period of two months starting from the inclusion of patients.

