2 groups of 75 persons will be formed. One group will have specific education using methodology of learning nests. The other group will be a control group not subject to this specific education. To evaluate, we propose a classical randomized controlled experimental (RCT) design, with randomization at the person-level. For outcome measures, we propose change in HbA1c, increase of social and emotional support and increase of linkage to clinical care. In addition to HbA1c, we propose measuring changes in systolic, diastolic blood pressure, and weight.

**Public health significance :** It is very important to find an education methodology adapted to the African context. This line of diabetes management is essential to improve the management of African diabetic patients.

**Sustainability plan:** If the evaluation of this methodology is conclusive, the Malian state will implement the methodology in the 22 diabetes units of the country.

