### **Methods for the randomization**

The patients will be selected from the list of diabetic patients followed in diabetes consultations of Bamako.

From this numbered list, a selection will be will randomly conducted with a number table to constitute the intervention group. We will verify that all the patients randomly selected to form this group meet the inclusion criteria of the group (see below).

The randomization list will be kept by the principal researchers of the survey.

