### **Non-inclusion criteria**

- Diabetic patients not carrying out their monitoring in diabetes units of the intervention area
- Patients followed in the diabetes units of the intervention area but not realizing their consultations regularly
- Patients with type 1 diabetes
- Severe complications within the preceding 3 months: infection, coronary complications, severe renal failure

- Concomitant illnesses threatening the functional or vital prognosis

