## STATISTICAL METHODS USED

The data will be analyzed by a medical epidemiologist with the Epi Info software.

Initially, we will proceed to the description of the included patients and compare the characteristics of both groups of patients to detect any differences at inclusion. These characteristics are expressed as percentage for qualitative variables and as mean and median and their dispersions parameters, respectively, standard deviation and interquartile 25 and 75. The comparison of characteristics between the two groups will be performed using appropriate tests, the exact X2 or Student's t-test. Then, a uni-variable analysis of variance analysis type will be conducted to identify variables to include in the multivariable explanatory models. The inclusion threshold chosen will be 0.25. Data will be expressed as means  $\pm$  SD unless indicated otherwise. Comparisons within groups were performed using analysis of variance by comparing the averages using the comparison test of averages or the Student's t-test.

The comparison between groups will be conducted by analysis of variance, using the Bonferroni correction where appropriate. The results will be statistically significant at  $p < 0.05$ .

**Direct beneficiaries in Mali:** The 150 diabetic patients directly reached by the activities / The 15 peer educators trained in the action areas selected in Mali. The 25 health agents of the action areas selected in Mali / Families and relatives of patients reached by animations (10 000 persons)

**Indirect beneficiaries in Mali :** All the diabetic patients of Mali (3% of the adult population) / All the health workers involved in the management of diabetes in Mali / The Malian health systems / The Malian population by reducing the risk factors of diabetes and increasing the quality of life

**Indirect beneficiaries in Africa:** Diabetic patients of French and English speaking African countries which will benefit from the methodology and tools developed

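### Control exposure to the peer-education programme is foreseeable, but the criteria leave two routes open and no direct record of exposure is planned

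*Supplement*

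**What the plan says.** **Allocation.** The scientific abstract (Method(s)) specifies a two-group trial "with randomization at the person-level". Under Methods for the randomization, "The patients will be selected from the list of diabetic patients followed in diabetes consultations of Bamako", and the intervention group is drawn at random from that list. Allocation is not by clinic.

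**Intended spread.** In Details of application, the item on social and emotional support says that keeping the booklet at home "will disseminate information within the family or/and in the social network of the trained patient". The item on linkage to clinical care has peer educators trained to go with patients to the facilities of the intervention area. It adds that patients may go with one another after the meetings.

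**Source of the educators.** The abstract says: "Peer educators and persons targeted by the project will be recruited through the local association of patients". The educators are themselves patients; the list of direct beneficiaries, under Statistical methods used, counts 15 of them.

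**Separation of the arms.** The abstract and the Comparison group section both keep controls out of the education programme. Booklets are handed out at the end of sessions, and the patient-circuit tool is given during them.

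**Criteria.** The inclusion criteria cover regular follow-up, type 2 diabetes, HbA1c of at least 8%, age 30 to 70, and agreement to the process and the measurements. The non-inclusion criteria cover patients such as "Diabetic patients not carrying out their monitoring in diabetes units of the intervention area", irregular attenders, type 1 diabetes, recent severe complications and serious concomitant illness. Neither list mentions peer educators or members of the same household.

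**Measurement.** The Chronogram has a Knowledge row from pre-inclusion to T12, with no description of the instrument. Nothing asks whether a control attended a session, saw a booklet or was accompanied by an educator.

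**The concern.** The main objective compares peer education plus usual care with usual care alone. If some controls receive part of the education, the two arms become more alike and the estimated HbA1c difference shrinks. Here the routes are foreseeable: the arms share consultations, booklets are meant to circulate at home and among acquaintances, and educators are present in the facilities.

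Two routes run through eligibility. An educator on the clinic list with HbA1c of 8% or more could be drawn as a control after being trained in the method. Two spouses could be split between the arms, so that the control lives with the booklet.

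The stake is a false negative, or an understated benefit, in a trial whose result is meant to decide roll-out to 22 diabetes units. Without an exposure record, a small or null difference would be hard to attribute either to the programme or to what reached the controls.

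**Working it through.** **Inputs from Calculation of the size of study:** difference 1 percentage point of HbA1c; reference-group SD 2.0; a second SD of 0.5; α 5%; power 80%; superiority; 60 evaluable per group; 20% loss to follow-up. Sidedness is not stated; two-sided is assumed.

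**Assumed:** the diluted share *c* of the effect. The documents give no exposure rate. A value of *c* = 20% could mean 20% of controls gaining the full benefit, or 40% gaining half of it (0.40 × 0.5 = 0.20).

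**Step 1. The plan's own figure.** n per arm = (s₁² + s₂²)(1.960 + 0.842)² / δ², where the squared bracket is 7.849.
- SD 2.0 in both arms: 8 × 7.849 / 1 = 62.8, so 63.
- SDs 2.0 and 0.5: 4.25 × 7.849 / 1 = 33.4, so 34.
- Stated: 60. Neither reading gives it exactly; the first is close (78.2% power at 60 per arm). The allowance for loss reproduces: 60 / 0.8 = 75.

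That mismatch is a separate matter. Here it means only that both SD readings should be shown. The calculation has no term for contamination.

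**Step 2. Power under dilution.** The true contrast becomes δ = 1 × (1 − c), and power = Φ(δ / SE − 1.960), with SE = √((s₁² + s₂²)/60).
- SD 2.0 in both arms: SE = √(8/60) = 0.365.
- SDs 2.0 and 0.5: SE = √(4.25/60) = 0.266.

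| c | δ | Power, SD 2.0 both | Power, SDs 2.0 and 0.5 |
|---|---|---|---|
| 0% | 1.0 | 78.2% | 96.4% |
| 10% | 0.9 | 69.3% | 92.2% |
| 20% | 0.8 | 59.1% | 85.2% |
| 30% | 0.7 | 48.3% | 74.9% |

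A t-based calculation for SD 2.0 gives 77.5, 68.6, 58.4 and 47.7%.

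**Step 3. Where the second reading drops below 80%.** It needs δ = 2.802 × 0.266 = 0.746, so *c* of about 25%.

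**Step 4. Evaluable patients per arm for 80% power at c = 20%.** Divide by 0.8² = 0.64: 62.8 / 0.64 = 98.1, so 99 with SD 2.0 in both arms; 33.4 / 0.64 = 52.1, so 53 with SDs 2.0 and 0.5.

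**Step 5. Scale of the educator route alone.** Each educator enrolled as a control is 1/75 = 1.3% of that arm. Even with full benefit, three of them would remove 3/75 = 0.04 of the 1-point difference.

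**The case against.** The case against has real force.

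- **Controls are separated from the programme.** They do not attend sessions, and the materials are tied to sessions. A reader might infer that nothing keeps the arms apart; the documents do not support that.
- **Knowledge is assessed at every visit.** A rise among controls would hint at spill-over, so it would be too strong to say that a null result could not be interpreted at all. But the instrument is undescribed, and knowledge can rise for other reasons. It is not an exposure record.
- **A relative's booklet is not the programme.** The protocol describes guided group work as the working part, so full transfer of the 1-point effect is an upper bound for each exposed control.
- **Few educators could become controls.** Each would have to be on the clinic list, meet the HbA1c and age criteria, be enrolled and be allocated to control. The count of 15 is not an exposure rate.
- **Shared association membership is not established for controls**, since patients are drawn from clinic lists. Only the shared consultations are firm.
- **Clinic staff.** The protocol says "All health workers of the area will be involved in the implementing and monitoring of the process". A reader might infer that the method spreads through staff to controls, but the text does not say that staff learn or deliver it; peer educators run the sessions.
- **The beneficiary count.** "The 150 diabetic patients directly reached by the activities" might be read as saying that controls receive the intervention. It is loose beneficiary wording, which could cover study examinations, and it does not override the two groups of 75 stated elsewhere.

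These points limit the size of the problem. They do not close the gap in the criteria or supply a direct record of exposure.

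**Conclusion.** The concern holds in a limited form. Allocation within shared consultations, with an intervention meant to pass information on to family and social networks, makes some control exposure likely. The criteria leave two avoidable routes open, and exposure is not recorded directly. The expected effect is bias of the HbA1c contrast towards no effect. Type I error is not inflated: if the programme has no effect, there is no benefit to pass on.

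The size cannot be derived from the documents. The power figures are illustrations over an assumed dilution of 0 to 30%, with 60 evaluable per arm and a two-sided 5% test. They depend heavily on the SD reading: at 20% dilution, power is about 58–59% with SD 2.0 in both arms and about 85% with SDs 2.0 and 0.5. The two eligibility routes alone may contribute little; the missing exposure record matters more for interpretation.

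A reader might go further and infer that individual randomisation is wrong here, or that the main objective cannot be answered. The documents support neither: controls stay out of the sessions, and the randomised comparison remains a valid, if possibly conservative, test.

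**What to change.** 1. **Non-inclusion criteria.** Add that trained peer educators, and anyone sharing a household with a patient already enrolled, are not included. Apply both before allocation, so that they act equally on the two arms.
2. **Exposure record.** At T3, T6 and T12, ask patients in both arms whether they attended a session, received or read a booklet, or were accompanied by a peer educator. Report the answers by arm next to the knowledge results. Use them to interpret the result only: self-reported exposure arises after randomisation and is open to recall and selection bias. The as-randomised comparison stays primary.

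**Cost.** A few otherwise eligible patients are lost from the clinic list, and three questions are added at visits that already take place. Individual randomisation, sample size and clinical care are unchanged.

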### **Methods for the randomization**

The patients will be selected from the list of diabetic patients followed in diabetes consultations of Bamako.

From this numbered list, a selection will be will randomly conducted with a number table to constitute the intervention group. We will verify that all the patients randomly selected to form this group meet the inclusion criteria of the group (see below).

The randomization list will be kept by the principal researchers of the survey.

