### **Eligibility criteria**

The study will be conducted among patients with type 2 diabetes followed in the decentralized diabetes units of Bamako. The methodology used to choose patients is described in the paragraph above. The recruitment will last during four months.

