### **Main judgment criteria**

The main judgement criteria on which the analysis will be done to comply with the superiority of the contribution of a group educational approach by the peer will be the evolution of the HbA1c from the inclusion to 1 year:

- the HbA1C gives a reliable reflection of the glycemic control that is not subject to short-term variations or bias caused by the social aspects that may influence self-evaluation of data;
- it responds directly to all practices that peer education aims to change (diet and exercise, self glucose monitoring, proper use of drugs etc ...)
- It is the most important physiological parameter to improve for people with diabetes, as it is related to the probability of occurrence of micro-and macro vascular complications.

For the measurement of glycated hemoglobin, the apparatus used will be the machine "Infopia". The preservation of the reagent throughout the study will be precisely monitored to avoid, with high temperatures, deterioration of reagents and therefore invalid action. The reagents will be stored in reagents storage structures of the laboratories of the health facilities involved. The measures will be undertaken by the laboratory assistants of the structures involved in the project and who will have been beforehand trained.

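### Patients, usual care and HbA1c measurement are spread over several Bamako diabetes units, but neither the draw nor the analysis takes unit into account: a small, cheaply avoided loss of precision

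*Supplement*

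**What the plan says.** The scientific abstract describes a single location: "It will be conducted in one site in one country Mali". The eligibility section shows that this means the city and not one clinic: "The study will be conducted among patients with type 2 diabetes followed in the decentralized diabetes units of Bamako". The inclusion and non-inclusion criteria also refer to units in the plural.

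Measurement of the primary outcome is decentralised in the same way. Under Main judgment criteria, "The reagents will be stored in reagents storage structures of the laboratories of the health facilities involved", and "The measures will be undertaken by the laboratory assistants of the structures involved in the project and who will have been beforehand trained". That section names one device type, identifies heat damage to reagents as a threat to valid readings, and says reagent preservation will be monitored. The Comparison group section describes usual care (counselling, examination, prescribing) as delivered in the diabetes consultations.

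The Methods for the randomization section starts from a numbered list of patients followed in the city's diabetes consultations and states: "From this numbered list, a selection will be will randomly conducted with a number table to constitute the intervention group". It mentions no strata, blocks or balance by unit. The abstract states that individuals are randomised, 75 to each group. Statistical methods used plans an analysis of variance between groups and multivariable models with variables screened at a threshold of 0.25; unit is not named in either. No section says that a patient's HbA1c must be read in the same laboratory, or on the same analyser, from inclusion to 12 months.

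**The concern.** Unit can affect the outcome in two ways. Local care may differ, so that HbA1c falls more in some units than in others. Local measurement may also differ, because of reagents that deteriorate at different rates or because of different operators. An unstratified draw lets the mix of units differ between arms, so part of any unit difference is carried into the arm comparison. An analysis without unit also leaves the between-unit variation in the error term, even if the arms happen to be balanced.

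The endpoint is change from inclusion to one year. A constant offset of one laboratory therefore cancels for a patient who is always measured there, and enters that patient's change in full if the laboratory changes in between.

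What is at stake is precision, and the credibility of the result if the unit mix turns out visibly uneven.

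**Working it through.** **Inputs from the protocol.** 75 per arm recruited; 60 per arm after 20% loss; target difference 1.0 HbA1c point; SD 2.0; alpha 5% (taken as two-sided); power 80%.

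**Assumptions.** The number and sizes of the Bamako units are not given, nor is any between-unit SD. I take 2 to 8 equal units, a between-unit SD (tau) of the outcome of 0.3, 0.5 or 1.0 point, and a total outcome SD of 2.0. I also assume that both arms come from the one list.

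**The plan's own figure.** n = 2 × (1.960 + 0.842)² × 2.0² / 1.0² = 62.8, so 63 per arm, against the 60 stated. At 60 the normal-approximation power is 78.2%. Inflation for loss reproduces: 60 / 0.80 = 75. The present point does not depend on the gap between 60 and 63; the 78.2% serves as a check on the simulation below.

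**Step 1: chance imbalance in one unit's share.** The 95% range is ±1.96 × √(2p(1−p)/75).

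| Unit's share p | 95% range |
|---|---|
| 1/3 | ±15.1 points |
| 1/4 | ±13.9 points |
| 1/6 | ±11.9 points |

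In simulated 75/75 allocation over 2, 4, 6 or 8 equal units, the largest between-arm difference in any unit's share had a median of 7–9 points and a 95th percentile of 15–17 points.

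**Step 2: resulting shift in the HbA1c difference.** With K equal units the SD of the shift is tau × √(2(1−1/K)/75). For K = 6 and tau = 1.0 this is √(2 × 0.833/75) = 0.149, which matches the simulated 0.149.

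| tau (assumed) | 95th percentile of the absolute shift, K = 2 to 8 |
|---|---|
| 0.3 | 0.08–0.09 point |
| 0.5 | 0.12–0.15 point |
| 1.0 | 0.27–0.32 point |

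For comparison, the standard error of the difference is 2.0 × √(2/75) = 0.33, or 2.0 × √(2/60) = 0.37 with 60 per arm.

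**Step 3: share of variance at issue.** tau²/2.0² is 0.09/4 = 2.25%, 0.25/4 = 6.25% and 1/4 = 25%. Only the last is large enough to matter for power.

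**Step 4: error rate and power.** Simulated with 60 per arm, effect 1.0, K = 2 and 6, and 2,500 runs per cell (simulation error on power about 0.8 point).

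| tau | Unstratified, no unit term | Unit fitted only | Drawn within unit and unit fitted |
|---|---|---|---|
| 0.3 or 0.5 | 78–80% | 78–80% | 78–79% |
| 1.0 | 78–81% | 86–87% | 89% |

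The first column agrees with the 78.2% from the formula. Type I error of the unstratified, unadjusted test was 4.2–5.7% across all cells. The simulation error there is √(0.05 × 0.95/2500) = 0.44 point, so this is compatible with 5%.

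**The case against.** The strongest reply is that unstratified randomisation of individuals is valid, and that stands. A reader might infer from the unit imbalance that the treatment estimate is biased or the test too liberal. The documents do not support that: individuals are randomised, the imbalance is ordinary sampling variation already reflected in the standard error, and the simulated type I error stays near 5%.

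A second reply is that the gain is negligible over much of the plausible range. This also stands: at tau of 0.3 or 0.5, power does not change beyond simulation error. A between-unit SD of 1.0 would be half the total SD, and nothing in the protocol shows it to be that large.

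Third, a reader might infer that switching between analysers will distort the primary comparison. The protocol gives no sign of this. It requires regular attendance at the units, so measurement in the usual unit is the natural reading, though it is not stated as a rule. Switching unrelated to arm would add noise only, and nothing suggests that it would differ by arm.

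Fourth, there are safeguards: one device type, operators trained beforehand, monitored reagent storage, a baseline comparison, and multivariable models that do not exclude unit. They reduce the risk. They do not balance the units, do not commit the analysis to unit, and include no stated check of HbA1c readings between laboratories.

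Finally, the randomization section describes only how the intervention group is drawn. A reader might infer that controls come from other units, which would make the imbalance systematic. The documents neither say nor imply this; the selection of controls is simply not described.

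**Conclusion.** The point holds as a minor one. Patients, care and HbA1c measurement are spread over several units, the draw is not balanced by unit, and unit is absent from the stated comparison. The consequence is a chance shift with a 95th percentile of about 0.08 to 0.32 HbA1c point, depending on the assumed between-unit SD, against a target of 1.0. Taking unit into account raises power from 78–81% to 89% if that SD is near 1.0, and has no detectable effect at 0.5 or below.

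These sizes rest on assumed unit numbers and shares, an assumed between-unit SD, and both arms coming from the same list. The absence of stratification is read from the protocol's silence. The change is worth making because it costs little, not because the trial would be invalid without it.

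**What to change.** 1. Sort the existing numbered list by diabetes unit and make the number-table draw within each unit, so that both arms come from the same units in equal proportion. This does not require eligibility to be known before the draw. The randomization section checks criteria after selection, and the Chronogram places randomization in month 6 and consent and laboratory tests in month 7. That order can be kept, or reconciled as a separate matter.
2. Name unit as a factor in the between-group HbA1c comparison, with a stated rule for pooling very small units.
3. State that each patient's HbA1c from T0 to T12 is read at the same facility on the same analyser where possible.

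Cost: slightly more work in preparing the list, one model term with a few degrees of freedom, and one conduct rule. The sample size does not change.
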